## Abstract

**Introduction:**

Cancer-related chronic pain is an important sequelae that damages the quality of life of breast cancer survivors. Pain neuroscience education and graded exposure to movement are therapeutic tools that have been shown to be effective in the management of chronic pain in other populations. However, there are no previous studies that combine them after breast cancer.

**Objective:**

To evaluate the effectiveness of an online physiotherapy focused-person program which combines pain neuroscience education and graded exposure to movement for quality of life improvement in breast cancer survivors.

**Methodology:**

This protocol is a randomized controlled trial with a sample size of 40 breast cancer survivors with pain in the last 6 months. Participants will be allocated to the experimental or control group using a fixed size block randomization method. The evaluator and statistician will be blinded to participant allocation. Participants in the experimental group will receive a 12-week intervention based on pain neuroscience education and therapeutic yoga as a graded exposure to movement exercise; participants in the control group will continue with their usual cancer-related symptoms care. Both groups will receive an education booklet. The main outcome will be quality of life, measured by the Functional Assessment of Cancer Therapy – Breast (FACT–B+4); secondary, four outcomes related to pain experience (catastrophising, self-efficacy, kinesiophobia and fear-avoidance behaviors) will be also assessed. All variables will be assessed by two blinded evaluators at four timepoints. A mixed-model analyses of variance ANOVA (2 × 4) will be used to study the effects of the treatment on the dependent variables. All statistical tests will be performed considering a confidence interval of 95%. SPSS program will be used for the data analysis.

**Discussion:**

This research is expected to contribute to breast cancer rehabilitation field. The proposed intervention is also expected to improve self-care skills related to chronic pain and to empower women regarding the management of their symptoms and quality of life.

**Clinical trial registration:**
https://clinicaltrials.gov/, NCT04965909.

## Introduction

1

Currently, chronic pain is one of the sequalae with the highest incidence in breast cancer survivors, seriously impacting their quality of life and making it difficult for them to reintegrate into society and their workplace (1**–**3). According to a biopsychosocial perspective (4), the chronification of pain must be understood as a complex and multifactorial process involving biological, psychological, emotional and social factors (5).

Together with the advances in the understanding of chronic pain, several therapeutic approaches have emerged. Among them, interventions based on pain neuroscience education (PNE) and graded exposure to movement (GEM) have reported important benefits for different chronic pain conditions (6–17). PNE is defined as a therapeutic tool implemented by a healthcare professional aimed at the empowerment of people related to their pain process management (18–21), while GEM applies movement following the “Twin Peaks” metaphor proposed by Butler (22) to get more functionality associated with less painful experiences. In this clinical trial therapeutic yoga will be applied as a graded movement intervention in conjunction with techniques of movement representation (GEM-Y). Therapeutic yoga has demonstrated to be an effective exercise for the improvement of quality of life in adults with cancer (23), for addressing other adverse effects on breast cancer survivors (24), and to manage symptoms in other chronic painpopulations (14, 15). In addition, yoga is a body–mind exercise that allows us to follow biopsychosocial approach (5) and to adjust easily the intensity of exercise to each individual context. PNE has been scarcely investigated in breast cancer survivors (25, 26), and for our knowledge the combination of PNE with GEM-Y has never been studied in this population. As breast cancer prevalence and survivorship rate is growing exponentially in transitioned countries, but also cancer-related symptoms (27), it would be helpful to investigate biopsychosocial interventions aiming to improve quality of life in this population.

Thus, the purpose of this clinical trial will be to evaluate if an intervention combining PNE and GEM-Y is more effective than usual care for quality of life and chronic pain improvements in breast cancer survivors.

## Methodology

2

### Study design

2.1

A randomized controlled clinical trial will be carried out according to the Consolidated Standards of Reporting Trials (CONSORT) Statement (28). The Template for Intervention, Description and Replication Checklist (TIDieR) (29) will be used as a guide to provide transparency and make the intervention replicable. Also, the Standard Protocol Items: Recommendations for Interventional Trials (SPIRIT) was followed to develop this protocol. The protocol of this study has been registered on clinicaltrials.org with the registry number: NCT04965909.

### Inclusion and exclusion criteria

2.2

Inclusion criteria: (1) Women aged between 18 and 65 years; (2) diagnosis of stage 0–III breast cancer; (3) primary treatment (surgery, radiotherapy and chemotherapy) completed at least 3 months ago but may still be receiving hormone therapy; (4) pain related to primary treatment in the last 6 months; (5) access to the Internet and an electronic device that allows the use of the applications used in this study and skills for their use or assistance from a close person who has them; (6) ability to communicate fluently verbally and in writing in the language of the research team (Spanish); and (7) approval to participate in the study by the coordinator of the health team that assisted during the course of cancer and its treatment.

Exclusion criteria: (1) another previous type of cancer or breast cancer recurrence in a period of less than 1 year; (2) medical diagnosis of a neurological or autoimmune disease that limits or prevents exercise; (3) some type of pathology that is associated with a contraindication to physical exercise; and (4) the diagnosis of serious psychiatric or neurologic disorders that do not allow the participant to follow orders.

### Sampling method and sample’s size calculation

2.3

For sampling, non-probabilistic convenience and snowball methods will be used. The sample size was calculated based on the change in FACT-B score between the treatment and control groups at week 12. According to a previous study (30), it is estimated that patients in the intervention group would have a difference in FACT-B score of 10.11 points or more compared to the control group (*F*-value = 4.86). This difference is above the minimal important difference reported for this measure (7–8 points) (31) and results in an expected partial Eta2 effect size of 0.049. Considering 2 groups, 4 measurements, a type I risk or α 0.05, type II risk or β 0.20 (study power of 80%) and an estimated dropout rate of 15%, a total of 40 participants (20 per group) are needed to be enrolled. Sample size was calculated using the G*Power software, version 3.1.9.7 (Heinrich-Heine University, Düsseldorf, Germany). Figure 1 shows the flow chart of the study.

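### The stated 80% power from 40 women for a 10.11-point FACT-B difference at week 12 is not supported by the protocol's own inputs

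*Protocol article*

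**What the plan says.** Protocol article, section 2.3, names a single contrast as the basis: "The sample size was calculated based on the change in FACT-B score between the treatment and control groups at week 12". From an earlier study it expects a "difference in FACT-B score of 10.11 points or more compared to the control group", with F = 4.86. It notes that this exceeds the minimal important difference of 7–8 points, and says that it "results in an expected partial Eta2 effect size of 0.049".

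The calculation then moves to another design: "Considering 2 groups, 4 measurements, a type I risk or α 0.05, type II risk or β 0.20 (study power of 80"%). With 15% dropout, G*Power 3.1.9.7 is reported to give 40 women, 20 per group.

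Section 2.8 makes the group-by-time interaction of a 2 × 4 mixed ANOVA the hypothesis of interest, at alpha 0.05. With two groups and four visits that test has 3 numerator degrees of freedom.

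**The concern.** A partial eta squared computed from a published F already reflects that F's error term. If it comes from one comparison of two groups, it describes a shift of about 0.45 SD. G*Power's default repeated-measures routine treats its f as an effect on the raw SD at each visit, and then credits the number of visits and their correlation. Entering the published value there counts precision that the trial will not have.

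This is the only power justification for the primary outcome. If power is well below 80%, a benefit of the size the protocol itself calls larger than the minimal important difference could easily be missed. A non-significant result could not then be read against the 80% that the protocol states.

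**Working it through.** **Inputs from section 2.3:** difference 10.11 points; F = 4.86; partial η² = 0.049; 2 groups; 4 measurements; alpha 0.05; power 80%; dropout 15%; 40 enrolled. Section 2.8 gives the test. **Not stated:** SD, degrees of freedom of F, within-person correlation r, epsilon, effect-size convention. These are assumed or varied below.

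**1. What the effect size means.**
- f² = 0.049/0.951 = 0.0515, so f = 0.227.
- Ratio of error to numerator df = F(1−η²)/η² = 4.86 × 0.951/0.049 = 94.3. With 1 numerator df this fits two groups with about 96 women in total (p = 0.03).
- On that reading d = 2f = 0.454, and the implied SD is 10.11/0.454 = 22.3 points.

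**2. Reproducing 40.** G*Power's default within-between interaction uses λ = f²·N·4·ε/(1−r), with df 3ε and 3(N−2)ε.
- r = 0.4, ε = 1, N = 34: λ = 0.0515 × 34 × 4/0.6 = 11.68, power 81%. Then 34/0.85 = 40.
- r = 0.5, ε = 0.75, N = 34: λ = 10.51, power 80%. Again 40.
- r = 0.5, ε = 1: N = 28, then about 33 enrolled.

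So this routine yields the stated figure, by multiplying f² by 4/0.6 = 6.7, or by 0.75 × 4/0.5 = 6.

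**3. What f = 0.227 stands for in that routine.** Here f² is the mean over the four visits of the squared interaction deviations, in raw-SD units. For a between-group difference δ at week 12, following three assumed profiles over T0–T3 as fractions of δ:

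| Profile | Interaction f when δ = 0.454 SD | δ at which f = 0.227 |
|---|---|---|
| 0, 0, 1, 1 | 0.113 | 20.2 points |
| 0, ½, 1, 1 | 0.094 | 24.4 points |
| 0, 1, 1, 1 | 0.098 | 23.3 points |

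Each δ is 10.11 × 0.227 divided by the middle column (unrounded). The calculation therefore has 80% power for roughly 20–24 points.

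**4. Power for 10.11 points with 34 evaluable women.**
- *Week-12 two-group contrast, unadjusted:* λ = f²·N = 0.0515 × 34 = 1.75, df 1 and 32, power 25%. With all 40 retained, 29%. 80% needs 156 evaluable.
- *Planned 3-df interaction, three profiles, ε = 1, d on the raw SD:*

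| r | Power, 34 evaluable |
|---|---|
| 0.4 | 19–26% |
| 0.5 | 22–31% |
| 0.7 | 35–49% |
| 0.8 | 50–68% |
| 0.85 | 64–81% |
| 0.9 | 82–95% |

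- *Same test, d on the SD of change:* the correlation cancels, and power is 22–31% whatever r is.
- *0.049 taken as an interaction partial η² in the SPSS convention:* λ = f²·(N−2)·3 = 0.0515 × 32 × 3 = 4.95, df 3 and 96, power 42% (49% with 40). 80% needs 74 evaluable, and 74/0.85 is about 88 enrolled.

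**5. Detectable difference.** For the unadjusted week-12 contrast with SD 22.3 and 34 evaluable, 80% power needs about 22 points, against the stated minimal important difference of 7–8.

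**The case against.** The strongest reply is that no single power figure can be called the true one. Section 2.3 gives no SD and no degrees of freedom for F, and does not say whether F came from raw, change or adjusted scores. The SD of 22.3 and the 96 women are back-calculated. A reader might infer that the trial's actual power is 25–30%. The document does not support that as a fact: it is one scenario, for an unadjusted week-12 comparison that section 2.8 does not plan. This part of the reply stands.

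Repeated measures can also add real power. If d is on the raw SD and r is 0.85–0.9, the interaction test reaches 80% (at 0.85 only for the most favourable of the three profiles). The one reliability figure given for the scale, an intraclass correlation of 0.986 in section 2.6.1, might seem to support so high a value. It is test–retest reliability, not a correlation across months of treatment and follow-up. Nor would such an r rescue the calculation: in the routine that reproduces 40, r has to be about 0.4, or 0.5 with a reduced epsilon; r = 0.8 would have given 14 evaluable women.

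The route to 40 is itself an inference. It fits exactly at the values shown, but a multivariate version of the interaction test at r = 0.5 comes close (32 evaluable, 38 enrolled). The absence of the G*Power settings from a condensed article is not a fault and is not raised as one. The point concerns a stated figure that does not follow from the stated inputs.

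**Conclusion.** The 80% claim is not supported. The effect size describes one week-12 contrast, and the sample size appears to treat it as a four-visit interaction effect on the raw SD, where it means about twice the stated difference or more. At the correlations that reproduce 40 (0.4–0.5), the planned interaction has about 19–31% power for 10.11 points with 34 evaluable women. The reading of 0.049 as an SPSS interaction effect gives 42%. The raw-SD reading gives 35–49% at r = 0.7 and 50–68% at r = 0.8. Only the raw-SD reading with r near 0.85–0.9 reaches 80%, and nothing in the protocol establishes it.

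The shortfall is firm over the other readings tried; its size is not. It depends on the unstated SD, df and correlation and, for the interaction, on the assumed profiles. A reader might also infer that the trial must be enlarged or relabelled a pilot. Neither follows: the error is in the stated power, and the protocol can keep its size and describe its precision correctly.

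**What to change.** In section 2.3, keep 40 women and withdraw the 80% claim. Recalculate from the earlier study's F with its degrees of freedom and SD, using the effect-size convention that matches how that F was obtained. State power and the difference detectable with 80% power for the group-by-time interaction planned in section 2.8, over a range of within-person correlations, with 34 evaluable and with all 40. If the week-12 difference remains the stated basis, give the same two figures for that contrast. Commit to reporting the week-12 between-group difference in FACT-B with its 95% CI beside the interaction test, so that a non-significant result can be judged by its precision.

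The cost is a revised paragraph and a less favourable stated power. No extra participants are needed, and the visits and the intervention do not change.

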**Figure 1 fig1:**
[figure not shown]
CONSORT flow diagram.

### Subjects’ recruitment

2.4

The sample for this study will be recruited through the dissemination of the project using social networks and with the collaboration of three Spanish breast cancer survivor support associations (Amama Sevilla, AGAMAMA and ASAMMA). Participation in the study will be voluntary. All participants will be facilitated by written informed consent that must be signed to be part of the clinical trial.

### Group assignment and masking

2.5

This study will have two groups (experimental and control). For assignment, a random method will be carried out using an online tool called ‘random allocation software’ (2.0 version). A stratified allocation will be applied according to the women’s age (≤45 years old or >45 years old). On each of the strata, a randomization will be carried out by blocks of constant size. The assignment sequence will be hidden from the evaluator and the study subjects through an automated assignment system. The preparation of the sequence, the inclusion of the individuals in each group and the assignment of the treatments will be carried out by different members of the research team. On the other hand, the evaluator and statistician will be blinded. Nonetheless, the therapist and subject will not be able to be blinded because of the type of intervention.

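### Constant-size blocks within two age strata leave a share of allocations certain to anyone who knows the block size and past allocations; randomly varying sizes would cut that share cheaply

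*Protocol article*

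**What the plan says.** Section 2.5 (Group assignment and masking) stratifies by age: "A stratified allocation will be applied according to the women’s age (≤45 years old or >45 years old"). It then fixes the block scheme within each stratum: "a randomization will be carried out by blocks of constant size". The abstract states the same choice: "Participants will be allocated to the experimental or control group using a fixed size block randomization method". The block size and the expected number of women per stratum are not given.

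On concealment and masking, section 2.5 says that "The assignment sequence will be hidden from the evaluator and the study subjects through an automated assignment system". It also assigns sequence preparation, inclusion and treatment assignment to different team members. It states that "the evaluator and statistician will be blinded" but that "the therapist and subject will not be able to be blinded because of the type of intervention".

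Section 2.3 sets the size of the trial: "a total of 40 participants (20 per group) are needed to be enrolled". It also specifies convenience and snowball sampling. Section 2.4 adds recruitment through social networks and three survivor associations.

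**The concern.** A permuted block must end balanced. Once one arm is used up within a block, every remaining place goes to the other arm. With a constant block size, an observer who has followed the stratum knows where each block ends, and so knows which places are forced. Hiding the list does not prevent this, because the inference uses allocations already made.

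In this trial each allocation becomes known to the woman and to the therapist. With snowball sampling, enrolled women may themselves be part of the referral route, so past allocations could reach the people who recruit. If someone who decides on inclusion or its timing can foresee the next arm, the choice of whom to include, or when, could depend on it. That would be selection bias in a trial of 40 women whose outcomes are self-completed questionnaires.

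**Working it through.** **Inputs.** Total 40, 20 per group (section 2.3). Two age strata and a constant block size (section 2.5). Assumed, because the article does not give them: block size *b* of 2, 4, 6 or 8; 20 women per stratum; women randomised one at a time; an observer who knows the block size and all past allocations in the stratum. The article states no predictability figure, so there is none to reproduce.

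**Step 1: certain allocations, constant blocks.** In a complete 1:1 block of size *b*, the expected share of places at which one arm is already exhausted is 2/(*b* + 2). Enumerating all balanced sequences confirms this:

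- *b* = 2: 2/4 = 50%
- *b* = 4: 2/6 = 33.3%
- *b* = 6: 2/8 = 25%
- *b* = 8: 2/10 = 20%

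With 20 women per stratum, blocks of 2 and 4 fill exactly, but blocks of 6 and 8 do not:

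- *b* = 6: three full blocks (18 places) plus 2 places. None of those 2 can be certain, so the share is 18 × 0.25 / 20 = 22.5%.
- *b* = 8: two full blocks (16 places) plus 4 places. None of those 4 can be certain, so the share is 16 × 0.20 / 20 = 16.0%.

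Over 40 women, the expected number of certain allocations is 20, 13.3, 9 and 6.4 for sizes 2, 4, 6 and 8.

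**Step 2: best-guess success, constant blocks.** The observer guesses the arm with more places left, with a success rate of one half when tied. For *b* = 4, the success rates at places 1 to 4 are 1/2, 2/3, 2/3 and 1, and their mean is 2.833/4 = 70.8%. With 20 per stratum, sizes 2, 4, 6 and 8 give 75%, 70.8%, 67.0% and 64.6%. An unpredictable sequence gives 50%.

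**Step 3: randomly varying sizes.** This was simulated with 20,000 sequences of 20 women, each block size equally likely. The observer knows the set of possible sizes and all past allocations, and updates by Bayes' rule.

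| Block sizes | Certain | Best-guess success |
|---|---|---|
| constant 4 | 33.3% | 70.8% |
| 2 and 4 | 10.5% | 71.9% |
| 4 and 6 | 5.8% | 68.5% |
| 2, 4 and 6 | 3.7% | 69.6% |
| 4, 6 and 8 | 2.4% | 67.1% |

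For sizes 4 and 6, 5.8% of 40 is about 2.3 women, against 13.3 with constant blocks of 4.

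**Step 4: sensitivity to the stratum split.** With 10 and 30 women, constant blocks of 4 give 30.1% certain and 69.5% best-guess success. Sizes 4 and 6 give 5.8% and 68.5%. The comparison does not depend on an even split.

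**Step 5: cost in balance.** An unfinished block of size *b* leaves an imbalance of at most *b*/2 in its stratum.

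- Constant 4: at most 2 per stratum, so 4 over two strata, or 18 v 22. Efficiency relative to 20 v 20 is 4 × 18 × 22 / 40² = 99.0%.
- Sizes 4 and 6: at most 3 per stratum, so 6 over two strata, or 17 v 23. Efficiency is 4 × 17 × 23 / 40² = 97.8%.

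These are worst cases over the possible stratum sizes.

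**The case against.** The strongest reply is that section 2.5 already contains real safeguards. The sequence sits in an automated system, three tasks are split between different people, and the evaluator and statistician are blinded. To exploit constant blocks, the person controlling inclusion would need the stratum, the order of randomisation within it, every earlier allocation there, and the block size, which the article does not publish. A woman knows her own arm, not the sequence, and the therapist is given no role in recruitment. This stands. A reader might infer that allocations are openly known and concealment has failed, but the article does not support that. It shows only that two parties are unblinded, and it does not say whether past allocations reach those who include women.

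The timing of randomisation also matters. Section 2.7 runs sessions in groups of 10 to 15, so randomising in batches is plausible, and predictability before inclusion would then be much smaller. The article does not say which is done. The figures above therefore hold only for one-by-one randomisation.

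A reader might also infer that varying the block size removes the problem for nothing. It does not: best-guess success hardly moves, it rises slightly with sizes 2 and 4, and the possible imbalance grows a little. Nor is it right that the analysis could never reveal or offset such selection. Section 2.8 plans baseline comparisons, every outcome is measured at T0, and the test of interest is group by time. Selection on measured variables could be partly seen or offset; selection on unmeasured factors could not be reliably repaired.

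Finally, the concealment sentence names the evaluator and participants but not the including staff. That is detail an article may leave to the full protocol, so it is not counted as a fault here.

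What remains is that the constant size is an explicit choice, stated twice, and a better one is available at little cost.

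**Conclusion.** The point holds as a cheap improvement. With constant blocks, 16% to 50% of allocations (33% at an assumed size of 4) are certain to someone who knows the block size and the stratum's history. Random sizes of 4 and 6 bring this to about 6%. The gain lies in removing most of the certain allocations; the best-guess rate falls only from 70.8% to about 68.5%, so predictability is reduced, not abolished.

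The size of the problem rests on assumptions that the article does not settle: the block size, about 20 women per stratum, one-by-one randomisation, and past allocations reaching those who decide on inclusion. The article gives no evidence that allocations have been or will be foreseen, and the point does not call the trial's validity into question.

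**What to change.** In section 2.5 and in the abstract, replace the constant block size with randomly permuted blocks of randomly varying size (for example 4 and 6 in random order) within each age stratum. Apply this to women not yet randomised. Withhold the sizes from everyone who recruits, includes or treats women until enrolment closes. Avoid sizes 2 and 4 as the pair: compared with constant blocks of 4, they leave best-guess success slightly higher.

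The cost is a regenerated list for the remaining allocations, two edited sentences, and a worst-case imbalance of 3 rather than 2 per stratum (17 v 23 instead of 18 v 22), which is about one percentage point of efficiency. If women are in fact randomised in batches after enrolment, one sentence saying so would answer most of the concern.
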